# IMAGINE study protocol of a clinical trial: a multi-center, investigator-blinded, randomized, 36-month, parallel-group to compare the effectiveness of motivational interview in rehabilitation of older stroke survivors

**DOI:** 10.1186/s12877-020-01694-6

**Published:** 2020-09-04

**Keywords:** Stroke, Geriatrics, Rehabilitation, Functional recovery, Physical activity, Motivational interviewing, Adherence, Clinical trial

## Abstract

**Background:**

Rehabilitation pathways are crucial to reduce stroke-related disability. Motivational Interviewing (MI), as a person-centered complex intervention, aimed to empower and motivate, and could be a resource to improve rehabilitation outcomes for older stroke survivors. The IMAGINE project aims to assess the impact of MI, as a complement to standard geriatric rehabilitation, on functional improvement at 30 days after admission, compared to standard geriatric rehabilitation alone, in persons admitted to geriatric rehabilitation after a stroke. Secondary objectives include assessing the impact of MI on physical activity and performance, self-efficacy, safety, cost-utility, participants’ experiences and functional status at 3 months.

**Methods:**

We will conduct a multicenter randomized clinical trial in three geriatric rehabilitation hospitals in Spain. Older adults after mild-moderate stroke without previous severe cognitive impairment or disability will be randomized into the control or intervention group (136 per group, total *N* = 272). The intervention group will receive 4 sessions of MI by trained nurses, including the design of a personalized rehabilitation plan agreed between stroke survivors and nurses based on stroke survivors´ goals, needs, preferences and capabilities. Main outcome will be the Functional Independence Measure (FIM). In-hospital physical activity will be measured through accelerometers and secondary outcomes using validated scales. The study includes a process evaluation and cost-utility analysis.

**Discussion:**

Final results are expected by end of 2020. This study will provide relevant information on the implementation of MI as a rehabilitation reinforcement tool in older stroke survivors. A potential reduction in post-stroke disability and dependence would increase person’s health-related quality of life and well-being and reduce health and social care costs. IMAGINE has the potential to inform practice and policymakers on how to move forward towards shared decision-making and shared responsibilities in the vulnerable population of older stroke survivors.

**Trial registration:**

ClinicalTrials.gov: NCT03434938, registered on January 2018.

## Background

Despite the positive advances obtained through acute treatments, stroke continues to be the leading cause of long-term disability in adults [1], reaching up to 40% of residual disability, and representing a huge burden for health and social systems, as well as for families [2].

Rehabilitation is crucial to reduce the gap between the persons’ disability and the demands of their environment [3]. In this sense, there are different interventions that focus on the different aspects of rehabilitation: some focus more on physical activity others on cognitive issues and some on regaining activities of daily living. Post-stroke rehabilitation entails a cyclical process, which includes: 1) identification of the person’s needs; 2) set of realistic and reachable goals; 3) implementing interventions according to these goals; and 4) follow-up, with potential revision of the goals and interventions [3]. Early rehabilitation [4, 5] and shared-goal setting between stroke survivors and healthcare professionals, based on the person’s preferences, values, previous routines and environment [6, 7], increase the odds of achieving better results [3]. Beneficial aspects include higher adherence to rehabilitation, increased personal satisfaction, shorter inpatient stays and greater goal attainment [6, 8]. This is also in line with the International Classification of Functioning, Disability and Health (ICF) [9], which promotes patient-professionals communication, and the terminology of which can be used to structure assessments, goals and plan interventions [10, 11]. However, patient participation in the process of goal setting is not standard clinical practice and even less so in geriatric rehabilitation, despite the fact that older persons need, due to their several comorbidities and various degrees of frailty, more guidance in defining their rehabilitation goals [12].

Further research has shown that psychological problems such as depression, apathy, anxiety, emotional and post-traumatic stress disorder are frequent complications following a stroke [13], reducing the motivation to engage in rehabilitation [13, 14]. Several studies have tested non-pharmacological interventions to reduce post-stroke psychological problems, such as cognitive-behavioral techniques and the improvement of social support networks [15, 16]. Nonetheless, most interventions are designed to be performed one month after the stroke and not during hospitalization in the acute phase, thus valuable time to begin and engage in rehabilitation is delayed [15]. Accordingly, new approaches are warranted.

Due to the population pyramid change and to the optimization of primary and secondary prevention treatments, the mean age of people with incident and fatal stroke has increased and is around 70.4 years old [2], [17]. Older adults have more frequently physical and mental comorbidities, and a pre-stroke reduced functional capacity that can be associated with social difficulties (i.e., living alone or with an old partner, low social support) which increase the risk of disability, institutionalization and death [18, 19]. Despite the high incidence of stroke in the aging population, older people with comorbidity and reduced functional ability have often been excluded from clinical studies precisely because of their high vulnerability and, therefore, it is necessary to increase research improving health outcomes in this segment of the population.

Motivational interviewing (MI) is a person-centered method where professionals and patients collaborate, utilizing a goal-oriented style of communication. This method gives particular attention to the language of change [20]. MI can be easily adapted to different healthcare settings and is known to strengthen personal motivation, empowerment, self-efficacy and commitment to specific personal goals by exploring and identifying the individual’s values and preferences [20]. MI has also demonstrated efficient in promoting physical activity, fostering treatment adherence [20, 21], and improving rehabilitation outcomes [20–22]. MI has been applied in frail older adults with mobility limitations, showing that it is safe and has a potential cost-effectiveness as a rehabilitative person-centered approach [23]. However, evidence of its effectiveness in older stroke survivors is lacking.

The IMAGINE study aims to investigate the effects of enriching usual geriatric rehabilitation with an adapted MI approach on different outcomes related to functional and clinical impact, persons’ satisfaction during hospitalization and cost-utility. We expect that the IMAGINE study will add a relevant contribution for the implementation of this intervention in older stroke survivors needing rehabilitation. Accordingly, this study should inform practice and policy makers on how to move forward towards shared decision making and shared responsibilities in a vulnerable population such as older stroke survivors [24]. With these aims, several hypothesis have been put forward:
MI, conducted during in-patient geriatric rehabilitation with older stroke survivors will result in an improvement in functional status at 30 days and 3 months, compared to standard geriatric rehabilitation alone.The MI intervention will induce a statistically and clinically significant increase in physical activity during the stay in the geriatric rehabilitation department, and an improvement in physical performance, compared to controls.The increase in physical activity and performance will be dose-correlated with the improvements in functional status.The intervention will result in a more favorable and satisfying experience with care during hospitalization for the participants, caregivers and professionals involved.Participants will increase their self-efficacy.The intervention will be a cost-effective strategy to improve participant outcomes at an acceptable cost (or even with no relevant incremental costs).The intervention will be safe for the stroke survivors. An increased number of adverse events potentially associated to geriatric rehabilitation and exercise will not be observed in the intervention group compared to control group

## Methods

### Design

Multicenter randomized clinical trial, with blinded outcome assessment.

### Setting

Geriatric rehabilitation units of three post-acute care hospitals in Catalonia, Spain.

### Population

Older stroke survivors admitted to one of the participating geriatric rehabilitation units. Inclusion and exclusion criteria are presented in Table 1.

**Table 1 Tab1:** Inclusion and exclusion criteria

Inclusion criteria	Exclusion criteria
1. Older adult (> 60 years old) 2. Admitted to the geriatric rehabilitation unit after a mild-moderate stroke (ischemic or hemorrhagic, stroke severity at admission assessed by National Institute of Health Stroke Severity (NIHSS) scale < 17 points) 3. Able to provide informed consent, personally or by caregiver.	1. Previous diagnosis of dementia (ascertained from medical records) 2. Severe post-stroke cognitive impairment (Pfeiffer SMPQ> 7 errors) 3. Persistent delirium (> 7 days) after admission in the rehabilitation unit 4. Previous severe disability in activities of daily living (pre-stroke Barthel index < 20/100 points) 5. Severe stroke which might limit recovery (NIHSS> 16) 6. Aphasia or other problems hampering communication 7. Advanced and/or terminal condition (life expectancy not exceeding 6 months).

### Randomization and blinding

After inclusion in the study and obtaining informed consent, participants will be randomized centrally to intervention or control group in a concealed allocation manner. That means that, in each study site, a researcher not involved in the assessments will access the OxMaR minimization software through a secure web access [25], and obtain the participant’s random treatment allocation. Randomization will be based on the minimization method, which has proven to provide balanced allocation of study participants in small trials, with respect to prognostic participant characteristics [26]. For each participant, treatment allocation will partially depend on the characteristics of the already enrolled participants [25]. The prognostic factors included in the minimization algorithm are: study site, gender (male or female), and type of stroke (ischemic or hemorrhagic). Due to the nature of the intervention, participants cannot be blinded to allocation, but will be strongly advised not to disclose their allocation status at any assessments. The assessments will be conducted by a healthcare professional (physiotherapist) blinded to treatment allocation. The assessors are encouraged to maintain the blind as far as possible, nonetheless, the assessor must report if the participant allocation was revealed.

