### Sample size calculation & statistical analysis

Sample size calculation is based on the results of previous RCTs assessing the effect of geriatric rehabilitation on improvement of the FIM. Accordingly, it is expected that geriatric rehabilitation will induce a 20 points improvement in FIM between admission and discharge [47]. This change has been established as “minimal clinically meaningful” improvement [48]. It is expected that MI plus geriatric rehabilitation will result in a “moderately relevant” clinical improvement in FIM, estimated to be 30 points. That is, MI will induce an additional improvement of 10 points (which corresponds to approximately 10% of total FIM score), compared to the control group. Considering a common standard deviation of 27.9 points in FIM, a 10% of drop-out rate at 30 days, and accepting an alfa risk of 0.05 and a beta risk of 0.2 in a bilateral contrast, we would need to include 136 stroke survivors in each branch (total sample = 272) to detect this improvement as statistically significant. Calculations were obtained using the GRANMO program [49].

Descriptive statistics will be presented for the overall characteristics of the study sample (intervention and control group) as frequencies and percentages for nominal or categorical variables and means and standard deviations for continuous ones. Baseline comparisons between treatment groups will be assessed as t-tests and chi-square tests, to check for potential imbalances in group composition and characteristics.

The effect of MI in the change in total FIM score between baseline and follow up (30 days) will be explored through a longitudinal repeated-measures mixed effects linear model, with the total FIM score as dependent variable, and a 2-level fixed factor accounting for the treatment group (MI or control). The model will adjust for clinically relevant covariates, such as age, gender and the amount of physical activity.

Group analyses will be carried out on an intention-to-treat principle. Missing data will be replaced by multiple imputations, after conducting explorations of the possible missingness mechanisms.

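### Allocation is minimised on site, gender and stroke type, but the primary model does not commit to site or stroke type; if they are omitted and prognostic, the test is conservative and loses some power

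*Protocol article*

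**What the plan says.** Under Randomization and blinding, the protocol article chooses minimisation to balance prognostic characteristics and lists the factors: "The prognostic factors included in the minimization algorithm are: study site, gender (male or female), and type of stroke (ischemic or hemorrhagic"). The Setting section gives three sites: "Geriatric rehabilitation units of three post-acute care hospitals in Catalonia, Spain".

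Under Sample size calculation & statistical analysis, the effect on change in FIM from baseline to 30 days "will be explored through a longitudinal repeated-measures mixed effects linear model, with the total FIM score as dependent variable", with "a 2-level fixed factor accounting for the treatment group (MI or control"). No time term or group-by-time term is named. On covariates the section says: "The model will adjust for clinically relevant covariates, such as age, gender and the amount of physical activity". Site and stroke type are not mentioned for the model. The same section also plans baseline tests: "Baseline comparisons between treatment groups will be assessed as t-tests and chi-square tests, to check for potential imbalances in group composition and characteristics".

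The sample size rests on two statements, "MI will induce an additional improvement of 10 points" and "Considering a common standard deviation of 27.9 points in FIM", with 10% drop-out, two-sided alpha 0.05 and 80% power. It is an unadjusted comparison of two means.

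**The concern.** Factors used to constrain allocation should normally enter the analysis. Minimisation makes the arms nearly equal on site and stroke type, so these factors contribute almost nothing to the chance difference between arms. A model without them still counts their variation as residual error. The reported standard error then exceeds the real sampling variability, confidence intervals are too wide, and the test rejects less often than its nominal 5%.

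The article itself calls these factors prognostic, yet the covariates it names overlap with the minimisation list only on gender. The trial is planned at about 80% power, and its Discussion names insufficient sample size and attrition as risks. Precision that the design has already paid for is therefore worth keeping.

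**Working it through.** **Inputs.** From Sample size calculation & statistical analysis: difference 10, SD 27.9, two-sided alpha 0.05, power 80%, drop-out 10%, 136 per arm. Not in the documents: R², the share of variance of the analysed FIM quantity explained by site and stroke type. It is an assumption here, varied from 0 to 0.30.

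**Step 1: the plan's own figure.** n = 2 × (27.9 × (1.960 + 0.842) / 10)² = 122.2 evaluable per arm. Dividing by 0.9 gives 135.8, rounded up to 136. The stated size is reproduced. Evaluable per arm: 136 × 0.9 = 122.4.

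**Step 2: standard error.** With the factors omitted, the model reports SE = 27.9 × √(2/122.4) = 3.566. With the factors balanced by design, the true SE is 3.566 × √(1 − R²). The overstatement is a factor of 1/√(1 − R²).

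**Step 3: error rate and power.**
- Type I error, omitted: 2 × (1 − Φ(1.960/√(1 − R²)))
- Power, omitted: Φ((10/3.566 − 1.960)/√(1 − R²)), where 10/3.566 = 2.804
- Power, included: Φ(2.804/√(1 − R²) − 1.960)

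Example at R² = 0.10, √0.90 = 0.9487:
- Type I error: 1.960/0.9487 = 2.066, giving 0.039.
- Power omitted: 0.844/0.9487 = 0.890, giving 81.3%.
- Power included: 2.804/0.9487 − 1.960 = 0.996, giving 84.0%.

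| Assumed R² | SE overstated | Type I error, omitted | Power, omitted | Power, included | Points forgone |
|---|---|---|---|---|---|
| 0 | 0% | 0.050 | 80.1% | 80.1% | 0 |
| 0.05 | 2.6% | 0.044 | 80.7% | 82.0% | 1.4 |
| 0.10 | 5.4% | 0.039 | 81.3% | 84.0% | 2.7 |
| 0.15 | 8.5% | 0.034 | 82.0% | 86.0% | 4.0 |
| 0.20 | 11.8% | 0.028 | 82.7% | 88.0% | 5.3 |
| 0.30 | 19.5% | 0.019 | 84.3% | 91.8% | 7.4 |

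**Step 4: simulation.** Minimisation on three sites, gender and stroke type was simulated with 244 evaluable patients, an assumed 0.8 assignment probability, 3000 runs per R² and one record per patient. At R² = 0.20 with the factors omitted, the mean model SE was 3.57 against an empirical SD of 3.23, and type I error was 0.031. Power was 82.4% omitted and 87.7% included. At R² = 0 the two models behaved alike. Simulated error rates carry a Monte Carlo error of about √(0.05 × 0.95/3000) = 0.004, so they confirm the direction and rough size, not the third decimal.

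**Step 5: does this carry over to the repeated-measures model?** One simulated two-visit data set was fitted with a random-intercept model, because the article does not say which term carries the effect.
- Effect as group-by-time, complete data: the SE was 2.6145 with or without main effects of site and stroke type. Main effects alone change nothing; only interactions of these factors with time could.
- Group factor alone, as literally worded: the SE fell from 3.29 to 3.19 when the factors were added.

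**The case against.** The strongest reply is that the covariates are introduced as examples. A reader might infer that the analysis ignores site and stroke type; the text does not say so. It leaves them undecided, and the final set may stand in a statistical analysis plan that is not shown. This reply stands against any claim of definite omission. It does not remove the point, because the article does name covariates and the set it names does not match the factors it balances on.

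A reader might also infer that the standard error is misstated as a matter of fact. That needs two things the documents do not establish: that the factors are omitted, and that they predict the analysed quantity. The Control group section describes routine rehabilitation in these centres as homogeneous, so the site effect could be small.

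Nor is there a threat of false positives or of hospital differences contaminating the comparison. Any error is conservative, and balance by site already keeps site differences out of the estimate; only the reported precision is affected.

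Two further inferences go too far. The baseline tests sit beside an open covariate list, but no sentence ties covariate selection to their p-values. Admission NIHSS would be a reasonable covariate, but it is not a minimisation factor, so its absence is no mismatch between design and analysis.

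Finally, the one-record formula does not transfer directly to a group-by-time contrast, as Step 5 shows. That objection stands and shapes the remedy.

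**Conclusion.** The point holds as a mismatch between allocation and stated analysis: the primary model does not commit to two of the three minimisation factors. The consequence is conditional and modest. For assumed R² of 5% to 15%, type I error lies between about 0.044 and 0.034, and the power forgone is 1.4 to 4.0 points. With no explanatory value the loss is zero; at R² of 30% it would be 7.4 points. These figures assume a single analysed value per patient with the planned SD, and near-perfect balance. The effect estimate is not biased, and power without the factors is still at least the planned 80% under the plan's own assumptions. It is a worthwhile improvement to the analysis wording, not a threat to the trial's validity.

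**What to change.** State in advance that the primary model includes every minimisation factor (site as a fixed effect, gender, stroke type) together with age, regardless of any imbalance seen at baseline. Then make the model form match, in one of two ways:

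- If the effect is group-by-time in the repeated-measures model, enter the minimisation factors with their time interactions, since main effects alone leave that contrast's precision unchanged with complete data.
- Otherwise, analyse 30-day FIM as the single outcome, with baseline FIM and the minimisation factors as covariates. Baseline FIM should not be added as a covariate while it also remains one of the repeated outcomes.

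Whether the amount of physical activity belongs in the model is a separate question that this change does not settle.

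The cost is wording only. Site, gender and stroke type are recorded for allocation, and age and baseline FIM are collected at admission. The 136 per arm need not change.

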### Intervention

The aim of the MI intervention, which will be integrated to the standard geriatric rehabilitation provided in the participating centers, is to empower, motivate and engage the person in planning and participating in the rehabilitation plan. The adaptation of the MI intervention is based on a previous pilot study carried out with older stroke survivors during geriatric rehabilitation, in one of the centers involved in the IMAGINE study [27]. Figure 1 shows the logic model of the intervention.

**Fig. 1 Fig1:**
[figure not shown]
Logic model of IMAGINE project

MI will be provided at the hospital ward, either in the person’s room or in an office nearby, according to their preferences and mobility. MI will be structured in four sessions: session 1 will be held one week from admission; session 2 within 6 days after the first session; session 3 at 1 week from the second session; and session 4 will be carried out pre-discharge.

The common goals for all sessions are:
To engage the stoke survivor in his/her care.Collaborative co-creation of a personalized rehabilitation plan, which would complement the routine geriatric rehabilitation.Reinforce engagement and adherence to the plan to maintain behavior change and functional improvement at 3 months.

The emphasis on each of the different goals will vary according to each MI session (see Fig. 2). Although this intervention focuses on physical training and functioning, during the MI sessions people will be also encouraged to perform other recreational, socializing, relaxing or similar activities during hospitalization, always according to individual preferences and objectives.

**Fig. 2 Fig2:**
[figure not shown]
Structure and main contents of MI sessions

MI involves the use of different core communication skills: 1) to ask open questions; 2) to affirm the person’s particular strengths, abilities, good intentions and efforts; 3) to use reflective listening; 4) to summarize the situation, and 5) to inform and advise with permission, which is useful to help people to reach their own conclusions about the relevance of any information the practitioner provides [20]. Each session will follow a semi-structured format to ensure homogeneity, while allowing tailoring. Content will generally include: 1) Creating engagement with the stroke survivor by exploring his/her preferences, values and goals, as well as his/her knowledge and expectations about stroke rehabilitation and recovery, 2) enhancing motivation by evoking strengths and abilities of the person, 3) follow-up and reinforcement, and 4) adapting the plan to the improved abilities and to home setting. As a practical milestone, during the second session the stroke survivor will establish tailored goals to complement standard rehabilitation, aimed at increasing involvement in self-care and daily living activities. When appropriate, in some cases debriefing with other professionals involved in the rehabilitation (physical therapists, occupational therapist or nursing staff) will be scheduled, to tailor and adjust the rehabilitation plan considering the functional situation. Figure 2 displays the structure of each session and specific criteria to conduct the additional interview between sessions three and four in case of external or internal modulators (which might have undermined the interviews). MI will be delivered by nurses trained through a certified MI course, and additional coaching by a psychiatrist who is a certified MI trainer will be offered to them throughout the intervention period (two group meetings per year and on demand individual sessions). During the study, quality control of the MI sessions using Motivational Interviewing Treatment Integrity (MITI) Code 3.1.1 [28] will be performed through video recording of a random selection of sessions.

